#### **Outcome measures:**

The **primary outcome** will be the number of healthy lifestyles adopted at 6 months. The criteria of successful adopting a healthy lifestyle are presented in Appendix 1.

**The secondary outcomes** will be the number of healthy lifestyles adopted at 12 months and improvement in health-related quality of life at 6 and 12 months.

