#### Follow-up assessment of behavioural changes at 3, 6, and 12 months

The success of the participants in achieving their targeted health-related lifestyle will be assessed through phone calls at 3, 6, and 12 months. If the participants report the successful adoption of a healthy lifestyle, the RA will encourage them to adopt another healthy lifestyle. Then, the RA will provide participants with brief healthcare advice (approximately 5 minutes) and send via WhatsApp/WeChat another 1-minute video focused on their newly chosen and desired health-related lifestyle.

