### **Sample size**

We used G\*Power to estimate the sample size based on the results of our pilot study conducted at an ED and a previous study using a brief smoking cessation intervention based on self-determination theory. The results of the pilot study showed an approximately 12% between-group difference in successfully adopting at least one healthy lifestyle at 6 months (the primary outcome of this proposed project). However, we opted for a more conservative effect size for our sample size calculation. Based on our previous large-scale RCT on a brief smoking cessation intervention based on self-determination theory, we expect a between-group difference of at least 5% ( $\geq 10\%$  in the intervention group vs.  $\leq 5\%$  in the control group) in the primary outcome at 6 months. To detect a significant between-group difference with a power of 80% at a significance level of 5% (two-tailed) in the proportion of participants modifying their health risk behaviours and/or adopting healthy lifestyles, 435 participants will be needed per group. To account for a potential attrition rate of 30% at the 6-month follow-up, we will recruit a total of 1,242 participants.

Based on the number of EDs visits (1.8 million) in Hong Kong between 2021 and 2022, we are confident that we will be able to recruit the required number of participants within 18 months.

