### **Data Analysis**

The baseline characteristics of the two groups will first be compared using the chi-square test for categorical variables and analysis of variance for continuous variables. An intention-to-treat analysis will be used by imputing all non-responses at follow-up by baseline values (i.e. assuming failure or no change after the intervention), to yield more conservative effect size estimates.

SPSS for Windows (SPSS version 26.0; IBM Corp., Armonk, NY, USA) will be used for the quantitative data analysis. Descriptive statistics will be used to calculate the mean, standard deviation, and frequency of the demographic and health-risk behaviour data. The primary analysis including the main effect, i.e., behavioural changes at 6 months in the intervention group versus those in the control group, will be performed using a chi-square test or Fisher's exact test. The secondary analyses will (1) assess the main effect adjusted for baseline differences, (2) assess the secondary outcomes (health-related quality of life) at 6 and 12 months, and (3) construct a generalised estimating equation model (GEE). The GEE model will be used to calculate the adjusted odds ratios for the self-reported the number of healthy lifestyles engaged in, after adjusting for the baseline demographic and clinical characteristics that show significant differences, and the within-subjects effect of the repeated-measure outcomes (6 and 12 months).

We will conduct a cost-effectiveness analysis (CEA) using standard methods. The CEA will be populated using empirical 12-month RCT data. An ingredients approach will be used to estimate the cost of the intervention programme, including that of the intervention material (e.g., leaflets and videos), the administration cost, and the time taken to deliver the intervention. The health effectiveness outcomes will include the number of participants who have adopted healthy lifestyles at 6 and 12 months and their QALYs.

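### The protocol names two different primary outcomes, a count and a yes/no proportion, and its stated 80% power belongs only to the yes/no version.

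*Protocol*

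**What the plan says.** The Protocol describes the primary result in several places, and they differ.

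- **Outcome measures:** the primary outcome "will be the number of healthy lifestyles adopted at 6 months". With four behaviours in Appendix 1, this is a count from 0 to 4 per participant. The interview plan at the end of the analysis section uses it in that sense, selecting participants with higher and lower numbers.
- **Sample size, pilot result:** the 12% difference is for "successfully adopting at least one healthy lifestyle at 6 months (the primary outcome of this proposed project"). This is a yes/no variable, and it carries the label of primary outcome.
- **Sample size, calculation:** power is computed for a difference "in the proportion of participants modifying their health risk behaviours and/or adopting healthy lifestyles", at 10% vs 5%.
- **Data Analysis, primary analysis:** the comparison of behavioural changes at 6 months "will be performed using a chi-square test or Fisher's exact test". The variable is not named.
- **Data Analysis, secondary analyses:** "The GEE model will be used to calculate the adjusted odds ratios for the self-reported the number of healthy lifestyles engaged in".
- **Hypothesis to be tested:** a higher proportion of individuals in the intervention group will adopt healthy lifestyles.

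No section says that the count will be dichotomised, or which version decides the trial.

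**The concern.** A confirmatory trial needs one variable on which it is judged. Here two variables hold that position. Both can be put through a chi-square test: one as a 2×2 table of adopters and non-adopters, the other as a 2×K table of the count. The two tables can disagree about significance, and nothing in the protocol settles which one counts. The analyst could therefore choose after seeing the data, or be suspected of having chosen.

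The sample size is also tied to only one of the two. If the count is the real primary outcome, the protocol has no power statement for it, because it gives no expected mean difference, SD or distribution.

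The same looseness affects the secondary model. A count gives an odds ratio only through an ordinal model or an adopted-out-of-at-risk model, and none is named. The model also refers to lifestyles engaged in, which can be read to include behaviours that were already healthy at entry; that is not the same as lifestyles adopted.

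**Working it through.** **1. Reproduce the stated sample size.** Inputs from Sample size: 10% vs 5%, 80% power, two-sided 5%. The allocation is 1:1. Pooled two-proportion formula, no continuity correction:

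n = [1.960·√(2·0.075·0.925) + 0.842·√(0.10·0.90 + 0.05·0.95)]² / 0.05²

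= [1.960·√0.13875 + 0.842·√0.1375]² / 0.0025 = 434.4, rounded up to **435 per group**.

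This is an exact match, with power 80.1% at 435 analysed per group. For attrition, 870 / 0.70 = 1,242.9 against the stated 1,242, a rounding difference. The arithmetic is sound, and it is arithmetic for a yes/no outcome.

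**2. What follows for the count.** Nothing follows from the protocol's own figures. As an illustration, keep 10% vs 5% adopting at least one lifestyle and assume that a share s of adopters take up exactly two. Then the mean is p(1+s) and the mean square is p(1+3s). For a comparison of means:

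| s (assumed) | Mean difference | SD | Needed per group | Power at 435 |
|---|---|---|---|---|
| 0 | 0.050 | 0.262 | 432 | 80% |
| 0.1 | 0.055 | 0.300 | 467 | 77% |
| 0.3 | 0.065 | 0.363 | 491 | 75% |
| 0.5 | 0.075 | 0.416 | 485 | 76% |

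With the same share s in both arms, a test of mean counts loses at most about 5 percentage points.

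**3. The count as an unordered table.** The noncentrality for 10% vs 5% at 435 per group is 0.05² / (2·0.075·0.925/435) = 7.84. If the same noncentrality is spread over more categories, power is 80% on 1 df, 71% on 2 df, 64% on 3 df and 59% on 4 df.

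**4. Simulation of the versions side by side.** 4,000 trials, 435 per arm, 5% vs 10% adopting at least one. Assumed split of 1/2/3/4 risk behaviours at baseline: 41.5/40/15/3.5%. The first figure is (80.3 − 47.0)/80.3 from the population survey in the Introduction; the others are assumptions. Each at-risk behaviour is taken up independently (about 2.8% per behaviour in the control arm).

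| Analysis | Power |
|---|---|
| At least one, two-proportion test | 82.1% |
| Count, unordered 2×K chi-square | 73.2% |
| Count, comparison of means | 83.0% |

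In a repeat run, the 2×2 and 2×K tests gave opposite significance verdicts in 8.5% of trials. In another, 84% of trials had a 2×K table with an expected cell below 5, where Fisher's exact test might be used instead. The 73% is therefore indicative only.

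**The case against.** The strongest reply is that the intention is clear. The hypothesis speaks of a proportion, the sample size is for a proportion, one cost-effectiveness measure is the number of participants who have adopted healthy lifestyles, and the named tests suit a 2×2 table. On that view the count is loose wording. This supports the choice of fix, but it does not remove the conflict: the outcome section defines a number, the 12-month secondary outcome repeats it, and the interview plan uses it as a number per person. A statistical analysis plan not shown here may pick one version, but the protocol would still label two.

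Four stronger readings are tempting and should not be drawn.

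- **That the chi-square test can be run only on the yes/no version.** It can be run on a 2×K table. It would then ignore the order of the count, and it is not what was powered.
- **That the trial is underpowered if the count is primary.** An analysis that uses the order of the count loses little or nothing in the calculations above. The loss belongs to the unordered table and rests on an assumed distribution.
- **That the arms are assessed differently.** The follow-up section states that "The success of the participants in achieving their targeted health-related lifestyle will be assessed through phone calls", and choosing a goal is described only for the intervention arm. But that text sits under the intervention group and concerns moving on to a next goal. Controls are assessed on the same schedule, the questionnaire covers all four behaviours, and Appendix 1 sets success behaviour by behaviour.
- **That the secondary model would be biased by baseline healthy behaviours.** Randomisation balances these in expectation, so the cost is precision and clarity of meaning. The model is secondary, and its link function could be left to an analysis plan.

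It is also fair to say that modifying a behaviour and adopting a lifestyle may coincide, since the Appendix 1 success criteria largely mirror the risk criteria. The powered wording is loose, but not certainly broader.

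**Conclusion.** The point holds as an inconsistency in the current text: one label, two variables, and a primary test that does not name its variable. The 80% power at 435 per group is correct for the yes/no outcome and is not established for the count.

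The size of the power consequence depends on the test. It is about 82% down to 73% for an unordered table under the assumed distribution, and little or nothing for an ordered analysis. The 8.5% rate of conflicting verdicts rests on the same assumptions, but it shows that the choice of version can change the conclusion. That open choice, more than any loss of power, is the reason to correct the text before data are seen.

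**What to change.** Use one primary variable, in the same words, under Sample size, Outcome measures and Data Analysis: the proportion of participants who at 6 months meet the Appendix 1 success criterion for at least one behaviour that was at risk at baseline. This agrees with the hypothesis, the sample size and the chi-square test. At the planning rates the smallest expected cell is 435 × 0.075 = 32.6, so the chi-square test is adequate for it.

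Then:

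- replace the powered wording ("in the proportion of participants modifying their health risk behaviours and/or adopting healthy lifestyles") with that definition;
- make the number of lifestyles adopted a secondary outcome;
- in the GEE, use lifestyles adopted instead of engaged in, and name an ordinal logit model or an events/trials logit model (adopted out of those at risk at baseline), so that the odds ratio is defined.

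The cost is wording only: no new data, and 435 per group and 1,242 in total are unchanged.

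If the sponsor prefers the count as primary, that is also defensible. It must then state the expected difference and SD, name an ordered or count analysis, and restate the power.

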The receipt of medical attention at an ED by a person in physical discomfort can serve as an excellent 'teachable moment' because it provides an invaluable opportunity to initiate a healthy lifestyle. People who consult a doctor in an ED are more likely to modify their risk behaviours to improve their health. According to the Hospital Authority Annual Report, there were 1.8 million ED visits in Hong Kong between 2021 and 2022. More than half of all ED visits were triaged as semi-urgent (level 4) or non-urgent (level 5), and most of the patients were discharged home after receiving medical attention. A previous study found that 86.6% of patients admitted to and discharged from the ED on the same day had a high risk of NCDs, such as blood pressure exceeding 160/100 mmHg before discharge. Furthermore, more than 75% of these patients did not receive any referral or follow-up care. The proposed project will address the gaps in the literature and will align with the Health Bureau's thematic priority B-0002: 'Develop and test novel approaches for enhancing prevention, early diagnosis, treatment, and recovery/ rehabilitation from major NCD'.

Aim and Hypotheses to be Tested:

Aim

To examine the effectiveness of a general health promotion intervention based on self-determination theory in helping ED attendees adopt a healthy lifestyle.

Hypothesis to be tested

We hypothesise that a higher proportion of individuals in the intervention group will adopt healthy lifestyles and have a better health-related quality of life than those in the control group at 6- and 12-month follow-ups.

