### Randomisation and allocation concealment

To prevent the potential risk of treatment contamination within the ED, randomisation will not be performed there. Instead, the research assistant (RA) will input baseline data collected at the ED directly into the web-based trial entry form linked to a computerised database. Subsequently, randomisation will be performed at the principal investigator's institution by an independent statistician who will have no other involvement in the study. Stratified block randomisation with 1:1 allocation will be conducted using varying block sizes of 4–10 to achieve an appropriate balance of participant numbers between the intervention and control groups and to optimise allocation concealment.

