## **Recruitment**

### **At the EDs**

We will obtain ethical approval from the institutional review boards of the five hospitals. **All** potential participants will be approached by emergency nurses before being discharged from the EDs. These nurses will provide potential participants with a leaflet detailing the nature, purpose, design, procedures, and potential benefits and risks of the study. Subsequently, the emergency nurses will refer the potential participants to the RA. Informed written consent will be obtained from all participants. Participants will be assured that their participation will be voluntary, with no prejudice attached to refusal, and that the information provided by them will be kept confidential. A baseline assessment will be performed using questionnaires. Then, participants will be informed that they will receive a telephone call from an RA within 3 days to evaluate their potential health-risk behaviours and provide them with appropriate health advice to adopt healthy lifestyles. In addition, the participants will be provided a Practical Resource Hub for Healthy Life leaflet (Appendix 2) containing information on various applications, including (i) 'Move Your Body', (ii) 'Eat Healthy', (iii) 'Live Alcohol Free', and (iv) 'Stay Away from Tobacco', which were developed by the Hong Kong Department of Health.

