#### Subjects

Chinese adults who attend one of the five EDs in various clusters in Hong Kong because of physical discomfort and if they meet the following criteria will be invited to participate. The inclusion criteria will be as follows: (1) being aged  $\geq 18$  years, (2) being triaged as semi-urgent (level 4) or non-urgent (level 5) and discharged home on the same day after receiving medical attention, (3) having at least one health risk behaviour (tobacco use, harmful alcohol consumption, unhealthy diet, and physical inactivity), and (4) owning a smartphone and having an ability to use instant messaging applications (e.g. WhatsApp or WeChat). The Exclusion criteria will be as follows: (1) having a poor cognitive state or mental illness and (2) being diagnosed with NCDs and undergoing regular follow-ups in outpatient clinics, and (3) participating in another related study.

The specific criteria for each health risk behaviour are listed in Appendix 1. People who do not have a smartphone or use WhatsApp/WeChat (unlikely in Hong Kong) will be provided brief advice and a Practical Resource Hub for Healthy Life leaflet on healthy lifestyles but will be excluded from the study.

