### **Data processing and analysis**

#### **Instruments:**

We will use available objective assessment tools to supplement the participants' self-reported outcomes to determine changes in their health-risk behaviours after the intervention. For verifying smoking cessation, we will use the biochemically validated 7-day point prevalence of abstinence, determined by a saliva cotinine level of  $<115$  ng/ml and an exhaled carbon monoxide level below  $<4$  ppm. Only those who meet both these criteria will be regarded as biochemically validated abstinent individuals; otherwise, the participants will be considered to have failed the validation. HK\$200 supermarket coupon being the incentive for completing biochemical validations

**A behavioural risk-factor questionnaire** will be used as the patient-report outcome measure to collect data on eligible participants' demographic and health-risk behaviours (tobacco use, binge drinking, unhealthy diet and physical inactivity) at baseline and at 3, 6, and 12 months. Moreover, participants' blood pressure and body mass index will be documented. This questionnaire was used to investigate multiple health-risk behaviours among Chinese adults in Hong Kong in 2021.

**The EuroQoL 5-Dimension 5-level (EQ-5D-5L)** will be used to assess the participants' health-related quality of life at baseline, 6 months, and 12 months. The psychometric properties of the Chinese version of the EQ-5D-5L were tested, and the findings indicate that this tool is a valid, reliable, and sensitive measure of health-related quality of life. A Chinese-specific EQ-5D-5L value set will enable the calculation of health utility scores applicable to the Chinese population and quality-adjusted life-years (QALYs) for conducting cost-effectiveness analysis.

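### Quality of life is worded as improvement, and the only earlier EQ-5D-5L is the one taken at the emergency department visit; comparing follow-up utility and QALYs with adjustment for that score is more precise and costs nothing

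*Protocol*

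**What the plan says.** **Outcome.** Protocol, Outcome measures, lists as a secondary outcome "improvement in health-related quality of life at 6 and 12 months". It does not say from what reference improvement is counted.

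**Hypothesis.** Protocol, Hypothesis to be tested, expects the intervention group to "have a better health-related quality of life than those in the control group at 6- and 12-month follow-ups".

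**Schedule.** Protocol, Instruments, has the EQ-5D-5L measure "health-related quality of life at baseline, 6 months, and 12 months". The behavioural questionnaire is also given at 3 months; the EQ-5D-5L is not.

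**Where baseline is taken.** Under Randomisation and allocation concealment, "the research assistant (RA) will input baseline data collected at the ED directly into the web-based trial entry form", and randomisation follows. The recruitment section for the EDs says "A baseline assessment will be performed using questionnaires". The Subjects section describes participants as "Chinese adults who attend one of the five EDs in various clusters in Hong Kong because of physical discomfort", triaged at level 4 or 5 and sent home the same day.

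**Analysis.** Protocol, Data Analysis, says that quality of life will be assessed at 6 and 12 months and names no model for it. Adjustment for baseline differences is named for the main effect and for the GEE on the number of healthy lifestyles, but not for quality of life or QALYs. On the cost-effectiveness analysis it says "The CEA will be populated using empirical 12-month RCT data" and refers to standard methods, without a rule for turning three utilities into a QALY.

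**The concern.** The outcome definition and the hypothesis do not match in wording. Improvement needs an earlier value, and at month 6 the only one is a score recorded while the person was in the ED with a physical complaint. Such a score may say little about health half a year later. Subtracting it in full then adds its variability to the outcome, whereas using it as a covariate takes from it only what it predicts.

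The same score enters the QALY. With no EQ-5D-5L between the ED visit and month 6, a straight line between those two points would carry the ED value across the first half-year. Any chance difference between arms in ED scores would pass into incremental QALYs, and so into the cost-effectiveness ratio, unless the estimate is adjusted for it.

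At stake are the precision of a secondary outcome and of the economic result. The primary outcome is not affected.

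**Working it through.** The protocol gives no utility, SD, correlation, QALY weight or power for quality of life, so there is no stated figure to reproduce. Inputs from the protocol are the EQ-5D-5L times (0, 6 and 12 months), 1:1 allocation after baseline, and 1,242 participants, hence 1,242 / 2 = 621 per arm. Everything else below is assumed and shown as a range.

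**1. Does recovery bias the contrast?** Let both arms have the same ED dip *d*, fully recovered by month 6, and let the intervention add *e*.
- Control change = *d*; intervention change = *d* + *e*; difference = *e*, whatever *d* is.
- Within the intervention arm, recovery makes up *d*/(*d* + *e*) of the change. For *d* from 0.05 to 0.20 and *e* from 0.01 to 0.03, this runs from 0.05/0.08 = 0.625 to 0.20/0.21 = 0.95.

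Recovery can therefore dominate change within an arm, but it cancels in expectation between arms.

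**2. Precision of a change score.** Let *k* be the ED SD divided by the follow-up SD, and *r* the correlation between the two scores. In units of the follow-up variance:
- change score: 1 + *k*² − 2*kr*
- baseline-adjusted follow-up: 1 − *r*²
- excess of the first over the second: (*k* − *r*)², which is never negative.

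| *k* | *r* | Variance ratio |
|---|---|---|
| 1 | 0.7 | 0.60 / 0.51 = 1.18 |
| 1 | 0.5 | 1.00 / 0.75 = 1.33 |
| 1 | 0.3 | 1.40 / 0.91 = 1.54 |
| 1.5 | 0.3 | 2.35 / 0.91 = 2.58 |

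**3. Weight of the ED score in a QALY.** With linear interpolation over two half-years:

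QALY = 0.5 × (u0 + u6)/2 + 0.5 × (u6 + u12)/2 = 0.25 u0 + 0.50 u6 + 0.25 u12.

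The 0.25 holds for a participant with both follow-ups.

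**4. Chance baseline imbalance.** SE of the baseline difference = SD × √(2/621) = SD × 0.05675. The QALY shift at 1.96 SE is 0.25 × 1.96 × SE.

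| Assumed SD | SE | 1.96 SE | QALY shift |
|---|---|---|---|
| 0.15 | 0.0085 | 0.0167 | 0.004 |
| 0.20 | 0.0114 | 0.0222 | 0.006 |
| 0.25 | 0.0142 | 0.0278 | 0.007 |

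For scale, a sustained utility effect of 0.01 to 0.03 at both follow-ups gives a QALY difference of 0.75 × *e* = 0.0075 to 0.0225.

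**The case against.** The strongest reply has four parts.

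*The comparison is randomised.* The design is between-subjects and the hypothesis is stated against control, so with a pre-randomisation baseline the arm difference in mean change and the arm difference in mean follow-up score estimate the same effect. This stands. A reader might infer that the outcome mainly measures recovery, or that recovery distorts the treatment effect. The documents do not support that: the first is true only of change within an arm, and the protocol nowhere plans to report that as an effect.

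*No change-score model is specified, and the choice of model may sit in an analysis plan not shown.* This stands in part. The protocol does not commit to analysing change. But the outcome definition belongs to the protocol, its wording differs from the hypothesis, and quality of life is left out where baseline adjustment is named for other outcomes.

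*The quarter weight is not in the protocol.* Correct. It follows from linear interpolation, which is an assumption here. It also applies only when both follow-ups are observed: Data Analysis replaces missing follow-up with baseline values, so the weight would be 1 for someone missing both.

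*The sizes depend on assumed inputs.* Also correct. At equal SDs and a correlation of 0.7 the precision loss is modest. The imbalance figures are 1.96-SE values (at SD 0.20, one SE gives 0.25 × 0.0114 = 0.003), and they are sampling error that a confidence interval already reflects. A reader might further suppose a large dip or a score limited to a single day. The documents give neither a recall period nor a baseline utility, and participants at triage level 4 or 5 who go home the same day may have only a small dip.

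**Conclusion.** The point holds as a mismatch of wording and an avoidable loss of precision, not as bias. The outcome is phrased as improvement, the only earlier reference is the ED-visit score, and the hypothesis asks for a comparison at follow-up.

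If improvement is analysed as a change score, its variance is about 1.2 to 1.5 times that of the adjusted comparison for correlations of 0.7 to 0.3 with equal SDs, and 2.6 times with an ED SD 1.5 times larger at correlation 0.3. If QALYs are interpolated linearly and left unadjusted, a chance baseline difference at 1.96 SE shifts the incremental QALY by about 0.004 to 0.007. These sizes rest on assumed SDs and correlations, the assumed interpolation rule, 621 per arm and complete follow-up.

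The consequence is limited to a secondary outcome and the cost-effectiveness analysis. The change is worth making because the adjusted analysis is, in large samples, never less precise and uses a score that is already collected.

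**What to change.** In Outcome measures, replace the improvement wording with EQ-5D-5L utility at 6 months and at 12 months. In Data Analysis, state that each is compared between arms with baseline utility as a covariate. This also brings the outcome into line with the hypothesis.

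For the cost-effectiveness analysis, state the rule used to build QALYs and estimate incremental QALYs by regression adjusted for baseline utility.

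Add that change from the ED score within an arm will not be interpreted as an intervention effect. A sensitivity analysis that assumes a short recovery after the ED visit is optional.

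The cost is a few lines of wording and one covariate in each model. No new data, visits or participants are needed.
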